### Pretreatment evaluations

2.7

Patients will sign the ICF and the TC, the anamnesis, the OHIP-14 questionnaire, and the data collection injury and questions regarding injury. Saliva and HSV secretions from all patients will also be collected for evaluation of inflammatory cytokines and saliva and HSV secretion for HSV quantification. Treatment will then be performed according to randomization.

### Anamnesis

2.8

Anamnesis will be performed in both groups. In addition to general patient health questions, demographic data (age, gender, marital status, occupation, educational level, living conditions, and salary), medical history data (primary complaint, current illness status, medical history, dental history, and medications) and will be asked when was the first infection and how many infections occurred within 1 year. The patient will be asked if there is a relationship between stress/begin of the injury and anxiety/begin of the injury.

### Experimental draw

2.9

Immediately prior to treatment of the herpes lesion the responsible investigator will remove and open 1 envelope (without changing the numerical sequence of the other envelopes) and perform the indicated procedure. In this way, the 24 patients will be allocated in the experimental and control groups (considering a drop out of 20%), as follows:

G1: Control group (n = 12) – Patients will receive the conventional treatment with acyclovir (described in detail in Section 2.11) and simulation of treatment with PDT (described in detail in Section 2.10).G2: Experimental group (n = 12) – Patients will be treated with PDT and will receive a placebo ointment simulating acyclovir cream.

### Treatment with photodynamic therapy

2.10

In group 2, patients will receive aPDT. The aPDT associates a photosensitive agent with a source of light and oxygen, to reduce the microbial load in places where there is no vesicle present.

The procedures will be performed as described:

1.If the lesions are in the vesicle phase, they will be ruptured with a sterile needle, and the overflow fluid will be cleaned with an absorbent paper taking care not to contaminate adjacent areas. The methylene blue solution at 0.005% concentration (Chimiolux; DMC, São Carlos, SP, Brazil) will be gently placed on the lesions.2.Application of methylene blue (0.05% Chimiolux 5 [DMC], purified water, and methylene blue) with a carpule syringe and needle (with stop and without bevel) on the lesions.3.One minute of preirradiation will be expected.^[29]^ The irradiations will be performed with the Laser Duo red laser diode (MMOptics, São Carlos, SP, Brazil) with a wavelength of 660 nm, with a power of 100 mW, energy density of 300 J/cm^2^, with energy of 3 J in the center of the lesion for 30 seconds.^[30]^ The laser head will be positioned in direct contact with the lesion perpendicular to the lesion.^[31]^4.It will be applied centrally to each isolated lesion that presents with fixed energy per point of 3 J.5.Wash in abundance with saline (saline solution) until the removal of the photosensitizer is complete.6.During the laser application both patient and operator will wear specific goggles to eye protection following the international security rules.7.Patients in group 2 will use placebo ointment as described in the following list.

The patients in group 1 (control-placebo of PDT) will receive an agent with the same vehicle as methylene blue to mimic irrigation with the photosensitizer and the laser will be switched off at the time of application.

The placebo PDT procedures will be performed on the lesion as described:

1.Application of methylene blue placebo with a Carpule syringe and needle (with stop and without bevel) inside the lesions.2.One minute of preirradiation will be expected.^[29]^3.The irradiations will be performed with the same device positioned in the same way and at the same time of application; however, the laser will be turned off. The beep sound will be recorded and turned on during application to blind treatment to the patient.4.It will be applied exactly as described in group 2. It will be washed in abundance with saline (saline solution) until the total removal of the placebo from the photosensitizer.5.During the simulation of the laser application both patient and operator will wear goggles (Table 1).

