## Discussion

3

Oral herpes lesions are very painful, bringing discomfort, and aesthetic impairment.^[6,10]^ The causes of recurrences are uncertain,^[39]^ the gold standard treatment is with antiviral acyclovir,^[9]^ and it is the most commonly used to prevent or suppress VHS^[10,14,40]^ but continued use of this drug may cause high viral resistance.^[7,10]^ Antiviral medications are most effective when the patient uses them for prodromal symptomatology and acyclovir is effective in reducing the duration and symptoms of infection, but the optimal dose is still unknown.^[9]^ Acyclovir may reduce the duration of symptoms but does not prevent recurrence.^[15]^ Because of these factors, aPDT is a good alternative for the treatment of herpetic lesions, which is a very promising treatment modality. Marotti et al^[20]^ in their study with 4 participants in the vesicle phase performed their perforation with a sterile needle to cause the flow of liquid. A 0.01% methylene-blue-soaked cotton ball was placed over the lesion for 5 minutes and the excess photosensitizer was removed. The lesions were irradiated with a wavelength of 660 nm, spot size 0.04 cm^2^ in continuous mode. The power was 40 mW, 2 minutes per point, with energy of 4.8 J (total energy of 19.2 J). After 24 hours, 72 hours, and 1 week, the same wavelength was used changing the parameters, with energy density of 3.8 J/cm^2^, 15 mW, and 0.6 J. No discomfort was reported throughout treatment and follow-up was 6 months with satisfactory results. Ramalho et al^[29]^ reported 2 cases, 1 in a 28-year-old female with a vesicle lesion, in which was punctured, its contents absorbed with absorbent paper, 0.005% methylene blue placed, waiting time of 5 minutes for the photosensitizer to act and the laser applied at a wavelength of 660 nm, with a power of 100 mW, 4.8 J, for 2 seconds per point. The following day, the lesion was already in the crusting phase. The 2nd case reported was from a female participant, 30 years old, who presented in the prodromal or tingle stage, and the participant reported that she had used acyclovir cream 5% when she had prodromal symptomatology. Methylene blue was placed over the macula and the same parameters as in the 1st case were used. The participant was instructed to continue acyclovir cream every 4 hours, and after 24 hours of PDT application, the macula was no longer detectable and herpes lesion did not develop. Marotti et al^[18]^ conducted a study with high intensity laser and PDT. The first case using PDT was in a 23-year-old female with herpetic lesions in the vesicle phase. They were punctured, dried with sterile gauze and 0.001% methylene blue and laser was applied with wavelength 660 nm, with fluency of 100 J/cm^2^, power of 100 mW, 28 seconds, 2.8 J of energy, spot size of 0.028 cm^2^ with total energy of 8.4 J after 24, 48, 72 hours, and 7 days after the 1st application. The parameters used were 20 J/cm^2^, power of 40 mW, 14 seconds per point with energy of 0.56 J per point. The other case was with a 24-year-old male participant using the same parameters as the previous case. Based on these cases and the cases in which Marotti et al^[20]^ used high intensity laser, the authors concluded that PDT has the advantage of low cost. It is based on the interaction of a photosensitizer and laser light in the tissue, causing selective cell damage, generating ROS.^[13]^ The photosensitizer (methylene blue) absorbs visible laser light at an appropriate wavelength (red 660 nm) from the ground state to the singlet state, which has a short lifespan. From this, the photosensitizer can lose energy through nonradioactive processes (phosphorescence) or generate ROS through 2 mechanisms: either by electron transfer, forming free radicals (type I reactions) or by transfer of energy to molecular oxygen forming singlet oxygen (type II reactions).^[21]^ The antimicrobial PDT is an effective alternative to the gold standard treatment, acyclovir, but there are no clinical studies yet to prove the efficacy of PDT in patients with recurrent herpes lesions, only case studies.

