In addition, the inflammatory markers TNF-α, IL-1β, IL-6, and IL-8 and IL-10 will be determined by 8-plex high sensitivity human cytokine per Millipore (Millipore Corporation, Billerica, MA), where Marques Filho et al^[43]^ found high levels of these cytokines in the crevicular fluid of patients with peri-implantitis. In the experimental group, methylene blue will be delicately placed and with a 1-minute wait for the photosensitizer to interact with the tissue according to Alvarenga et al.^[43]^ The parameters used for laser application will be performed according to Ramalho et al^[29]^ in case studies reported using 0.005% methylene blue photosensitizer, with the laser head in contact with the lesion, perpendicularly, 3 J energy for 30 seconds, with diode laser at 660 nm wavelength in a single session. Marotti^[20]^ used the laser at the same wavelength, with an energy density of 120 J/cm^2^, with a power of 40 mW, with 2 minutes per point and 4.8 J energy at each point and with 4 points around the lesion in herpes lesions in the vesicle phase, breaking them prior to the application of methylene blue, in which it was used at a concentration of 0.01% (the use of 0.005% is explained based on the large quantity of works with good results). The total energy delivered was 19.1 J. Twenty-four hours after the 1st application, the procedure was repeated, but with energy density of 3.8 J/cm^2^, 15 mW of power, with 0.6 J of energy at the same previously irradiated points, and these parameters were repeated after 72 hours and after a week. There was a decrease in the frequency of vesicle recurrence. De Paula Eduardo et al,^[13]^ found in a literature review that in cases where aPDT was indicated in the vesicle phase, there was a reduction in vesicle title as well as lesion duration. Decreased signs of infection and symptoms are reported within hours of aPDT application, provided they are used at a wavelength around 660 nm and with the appropriate photosensitizer. Based on these studies, we expect a reduction in the time of resolution of lesions, as well as the recurrence of lesions, providing a low cost alternative indicated for patients with viral resistance to the gold standard drug, acyclovir, and, offering an alternative in immunocompromised patients who have a high recurrence of herpetic lesions and in patients who should avoid drug administration by organ impairment where acyclovir is metabolized, as well as in healthy patients who have a high recurrence of lesions, decreasing discomfort.

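### Section 2.10 gives the methylene blue concentration as 0.005% in step 1 and 0.05% in step 2 of the same experimental procedure, a tenfold conflict

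*Protocol article*

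**What the plan says.** Section 2.10 of the protocol article lists the steps for the experimental arm. Step 1 opens with what is done when lesions are in the vesicle phase, and then says "The methylene blue solution at 0.005% concentration (Chimiolux; DMC, São Carlos, SP, Brazil) will be gently placed on the lesions". Step 2 says "Application of methylene blue (0.05% Chimiolux 5 [DMC], purified water, and methylene blue) with a carpule syringe". Both steps name a Chimiolux product from the same manufacturer.

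The Discussion uses only the lower figure for this trial. It says the laser parameters follow earlier work "in case studies reported using 0.005% methylene blue photosensitizer, with the laser head in contact with the lesion, perpendicularly, 3 J energy for 30 seconds". It also defends the choice of strength: "the use of 0.005% is explained based on the large quantity of works with good results". The other strengths mentioned there describe other published cases.

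The sham list in section 2.10 has one step in which the placebo liquid is applied. Section 2.3 admits lesions in the prodromal, vesicle, ulcer and crust stages.

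The light settings in section 2.10 are given "with a power of 100 mW, energy density of 300 J/cm^2" and "with energy of 3 J in the center of the lesion for 30 seconds", at 660 nm, with reference 30 cited for the irradiation. Table 1, which holds the treatment parameters, is not visible in the text available.

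**The concern.** The photosensitizer is one of the two active components of the experimental treatment, the other being the light. The investigator who opens the envelope treats from these numbered steps, and they give two strengths without explaining why there would be two.

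Two things are at stake. The first is patient exposure: someone following step 1 and someone following step 2 would apply solutions that differ tenfold. The second is interpretation. The comparison of resolution time with acyclovir is meaningful only if the experimental arm is one defined treatment that others could repeat. If the strength also varied with lesion stage, strength and stage could not be separated within the experimental arm, and stage at entry may itself bear on time to resolution.

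**Working it through.** **Concentration**

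| Place | Strength stated |
|---|---|
| Section 2.10, step 1 | 0.005% |
| Section 2.10, step 2 | 0.05% |
| Discussion, account of the parameters to be used | 0.005% |
| Discussion, rationale for the strength | 0.005% |

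Ratio: 0.05 / 0.005 = 10. If the percentages are weight per volume, which is an assumption because the article does not say, they correspond to 0.5 and 0.05 mg/mL. The ratio is the same on any common basis.

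**What the steps imply**

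- *One application.* Step 2 restates, with the syringe and needle, how the product in step 1 is put on. There is then one application with two incompatible strengths.
- *Two applications, with the vesicle condition governing all of step 1.* Vesicle-stage lesions receive 0.005% and then 0.05%. Prodromal, ulcer and crust lesions receive 0.05% only. The sham list has one liquid application, so a vesicle-stage control patient would have one application fewer than a vesicle-stage experimental patient.

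The text does not settle which reading is intended. Each leaves something to be corrected.

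**Light dose: the plan's own figure first**

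Inputs from section 2.10: power 100 mW = 0.100 W, time 30 s, energy density 300 J/cm².

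- Energy = power × time = 0.100 × 30 = 3.0 J, which reproduces the stated 3 J.
- Implied spot area = energy / energy density = 3 / 300 = 0.01 cm².

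The stated settings agree with one another, and the Discussion repeats 660 nm, 3 J and 30 s.

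**Light dose: the attribution**

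The Discussion says these settings follow a two-case report (reference 29). Earlier in the same section that report is described as "with a power of 100 mW, 4.8 J, for 2 seconds per point", with a wait of 5 minutes.

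- At 100 mW for 2 s the energy is 0.100 × 2 = 0.2 J, not 4.8 J.
- To deliver 4.8 J at 100 mW takes 4.8 / 0.100 = 48 s.

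So the description of the source is arithmetically inconsistent as well as different from the trial's settings. Section 2.10 cites reference 30 for the irradiation. It cites reference 29 only for the one-minute wait, which the Discussion credits to another source.

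**The case against.** The strongest reply is that this is probably a slip in one line. The figure 0.05% appears once, against 0.005% in step 1 and twice in the Discussion, once with a reason. Both steps name a product from the same manufacturer, the sham list has a single application step, and nothing says that a second application or a second strength was planned. Table 1 may state the value plainly.

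Much of this stands. It makes a slip plausible, and it means stage-dependent exposure can be put only as a possibility. It does not remove the conflict. A count of mentions does not establish which figure is right, step 2 is an operative instruction, and a table with one value would still disagree with one of the two steps. Nor is this a detail lost in condensing the protocol: the article prints both numbers.

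A reader might go further and infer that the light dose is also undefined, or that it departs from its source by the gap between 3 J and 4.8 J and between 30 s and 2 s. The documents do not support that. The trial's light settings are consistent with one another, and section 2.10 rests the irradiation on reference 30. The figures given for reference 29 cannot all be true, so they cannot measure a departure. Neither reference was available to check.

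**Conclusion.** The concentration conflict is real and must be corrected. Section 2.10 gives two strengths for the photosensitizer that differ by a factor of ten, and the Discussion supports only one of them by mention. The factor of ten applies to concentration alone.

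That exposure would differ by lesion stage, or that the sham would lack an application, holds only if steps 1 and 2 are separate applications, which the text leaves open. It would also be too strong to infer that the intervention was never decided: the Discussion's rationale suggests that a strength had been chosen, although it does not prove which step is in error.

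The light settings are a minor matter of attribution. The dose as written is coherent at 3 J per point, while the account of the case report it is said to follow is not.

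The conclusion rests on the article's text, with Table 1 and the cited sources unseen. It takes no view on which concentration is correct.

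**What to change.** Before the first patient is treated, the sponsor should reconcile steps 1 and 2 of section 2.10 with each other, with the Discussion and with Table 1. The revised text should:

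- state one consistent concentration specification for the photosensitizer, checked against the product label;
- say whether one or two applications are made, and whether this depends on lesion stage;
- match the sham list to the active procedure in number and order of applications.

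The clinical team decides the values. If anyone has already been treated, the strength actually used should be recorded for each patient.

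As a lesser correction, the Discussion should give the proper source for the light settings and for the one-minute wait, and should repair or drop the inconsistent figures quoted for the case report.

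The cost is a protocol clarification and a label check. Sample size, randomization, visits and analysis are unaffected.

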**Table 1 T1:**
[figure not shown]
Parameters used in photodynamic therapy.

### Treatment with acyclovir

2.11

Patients in group 1 (control): Following the simulation of treatment with aPDT, the patient will receive a catheter with acyclovir cream and will be advised to spread on the lesions 4 times a day for 7 days, in which will be their return for reevaluation. The same patient will be reevaluated after 1 month, 3 months, 6 months, and 1 year.

Patients in group G2 (experimental): The patients will perform the aPDT as described and will undergo the same procedures of the patients of group G1, that is, will receive a tube with a placebo cream simulating aciclovir and the same will be advised to spread the cream 4 times per day for 7 days. The patient will return for reassessment after 3 and 7 days and will be followed up after 1 month, 3 months, 6 months, and 1 year for recurrence evaluation.

All treatment proposed in group 1 (simulation of aPDT + delivery of aciclovir cream) in each patient will be concluded in a single session. Treatment for group 2 (aPDT + placebo cream) will also be completed in a single session. All possible adverse effects will be noted and qualified during the treatment protocol and maintenance period (3/3 months) using the questionnaire developed for this protocol. Adverse events will be reported in the results section of the manuscript and will be discussed. The Research Ethics Committee of the Universidade Nove de Julho (UNINOVE) will be notified of any change.

### Study variables and time

2.12

The primary study variable will be evaluation of the resolution time of the lesions in days (primary objective of the study). For this, a 15-day follow-up will be performed for this variable.

The secondary variables of the study will be

Follow-up of the recurrences of herpes simplex labialis (HSL) lesion at baseline (T0), 1 (T3), 6 months (T4), and 1 year (T5) follow-up periods.Presence of ballooning cells by exfoliative cytology at baseline (T0) and 3 (T1) days after injury.Evaluate if the amount of HSV-1 decreases after treatment with aPDT by Quantitative polymerase chain reaction q at the baseline (T0), 3 (T1), and 7 (T2).Evaluation of cytokines interleukin (IL)-6, IL-1β, IL-8, tumor necrosis factor alpha (TNF-α), and IL-10 by enzyme-linked immunosorbent assay method in nonstimulated saliva and HSL lesions in the baseline (T0), 3 (T1), 7 (T2), and 30 days after treatment (T3).To verify the presence of pain in HSL patients by HSL VAS at baseline (T0), 3 (T1), 7 (T2), and 30 days after treatment (T3).Check the temperature at the site of HSL lesion at baseline (T0), 3 (T1), 7 (T2), and 30 days after treatment (T3).Quality of life perception of HSL patients related to oral health will be assessed using the OHIP-14 questionnaire at baseline (T0) and 30 (T3) days after treatment.

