## Methods

2

This is a single-center randomized, double-blind, controlled, prospective trial consistent with the criteria for designing a clinical SPIRIT statement. The project will be submitted to the Research Ethics Committee of Universidade Nove de Julho (UNINOVE). After verbal and written explanation of the study, participants who agree to participate in the study will sign the informed consent form (ICF) and the term of consent (TC) for children under 12 to 18 years of age ([name]). The study will be conducted in accordance with the Declaration of Helsinki. The project will be registered at www.clinicaltrial.gov. Project receive grant from Brazilian National Council for Scientific and Technological Development - CNPq #165189/2019-3 (CNPq, Portuguese: Conselho Nacional de Desenvolvimento Científico e Tecnológico). Patients will be invited to attend the Dental Clinic of the University of Nove de Julho (UNINOVE), at city of São Paulo, Brazil, from January 2020 to August 2021 for PDT treatment and evaluation. The experimental design will consist of 2 groups. The sample will be composed of healthy patients who have herpes lesions in the vesicle or crust stage. The total time for lesion remission, ballooning cell verification, virus quantification at the site of injury, and saliva will be assessed. Samples (HSV secretion) will be collected at the injury site and saliva for the quantification of inflammatory cytokines. Pain, temperature, and recurrence of the lesion will be assessed at a 1-year follow-up. The OHIP-14 questionnaire will also be used to measure quality of life related to oral health. Patients will return in 3 days (T1), 7 days (T2), 30 days (T3), 6 months (T4), and 1 year (T5) for reevaluation. Every time there is recurrence of the lesion, the clinic will be invited for collection and verification of the lesion site (recurrence in the same place, it will be noted in the labial diagram by sextant) (Fig. 1).

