#### Presence of ballooning cells

2.13.3

Quantify the ballooning cells by means of exfoliative cytology.^[32]^

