#### Collection of ballooning cells for exfoliative cytology

2.13.4

The swab on the lesion of the exfoliative cytology kit of the female swab specimen collection kit (Qiagen, Hilden, Germany) will be gently passed, made the smear on a slide for microscopic examination.

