### Statistical analysis

2.14

Statistical analysis will be performed using only the data obtained from the patients who complete the study. The Kolmogorov–Smirnov test will be applied before the analysis of the normality of each parameter. The *t* test will be used to compare all means. All tests will be performed using Graphpad Prism 5 (Graphpad Software, San Diego, CA). Data will be presented on average and ±standard deviation. The level of significance will be set at *P* < .05.

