
This study will be a double-blind clinical trial with the goal of not inducing the researcher who will treat the patient to a positive aPDT result as well as to mask the participant's type of treatment. Blocked randomization was performed so that if there is any interruption of work for any reason, we will have groups with proportional numbers of participants, allowing comparison between them. After approval by the Research Ethics Committee of the Universidade Nove de Julho, patients will be invited to participate in the study by signing the ICF. If the lesions are in the vesicle stage, they will be topically anesthetized with 2% lidocaine gel, as directed by the Research Ethics Committee. Exfoliate cytology of the lesions will be performed as it is a simple and reliable method of confirming HSV infection, according to Barret et al. Microscopically we can observe changes in cytoplasm and nuclear structures. Lange et al,^[41]^ observed that cells exhibit a space between inclusion and the extended “bull's eye” cell membrane. In addition, he observed little frequency of ballooning cells, which are pathognomonic cells in herpes lesions.

Unstimulated saliva collection will be performed before treatment, 3, 7, and 30 days after the procedure, in both groups, to quantify the virus by qPCR and to evaluate the cytokines IL-6, IL-1β, IL-8, TNF-α, and IL-10. For HSV-1 amplification by qPCR, a set of HSVP1/HSVP2 primers will be used, which corresponds to DNA sequencing the eight human herpes virus described by Johnson et al. This primer amplifies HSV-1 subtypes, HSV-2, Epstein-Barr virus, and cytomegalovirus.^[32,33,42]^

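### Ballooning cells are a presence outcome in section 2.12 but a quantity in section 2.13.3, so the same slides can be significant in one form and not in the other (minor, one secondary endpoint)

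*Protocol article*

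**What the plan says.** Four places in the protocol article bear on this outcome.

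- **Section 2.12 (Study variables and time)** lists it as "Presence of ballooning cells by exfoliative cytology at baseline (T0) and 3 (T1) days after injury".
- **Section 2.13.3**, under a heading that again uses the word presence, has one sentence: "Quantify the ballooning cells by means of exfoliative cytology".
- **Section 2.13.4** describes the specimen: a swab of the lesion, "made the smear on a slide for microscopic examination". It gives no count unit, no number of cells to be read and no threshold for calling a slide positive.
- **Section 2.14 (Statistical analysis)** states "The *t* test will be used to compare all means", with results shown as mean and standard deviation. It names no method for a proportion.

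The Methods overview says only "The total time for lesion remission, ballooning cell verification, virus quantification at the site of injury, and saliva will be assessed". That wording is neutral between the two forms. The same overview fixes the visits: "Patients will return in 3 days (T1), 7 days (T2), 30 days (T3), 6 months (T4), and 1 year (T5) for reevaluation".

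**The concern.** Presence and quantity are different endpoints. A patient whose count falls from many cells to one has improved greatly on the count and not at all on presence. If section 2.12 governs, the stated test does not fit the outcome. If section 2.13.3 governs, section 2.12 misnames it. One of the two has to change.

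While both forms stand, either can be reported after the data are seen, and in a trial this small they will often not agree on significance.

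**Working it through.** **Inputs from the article.** Section 2.8 of the article's procedures plays no part here; the relevant inputs are 12 per group (section 2.1), significance at P < .05 (section 2.14, taken here as two-sided) and a t test of means (section 2.14). The 12 per group are the completers: 12 / (1 − 0.20) = 15 randomised per group, 30 in all, which matches section 2.5. The article states no figure for the ballooning-cell outcome, so there is none to reproduce.

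**Assumed inputs.** The article gives no counts. Counts per slide are taken as negative binomial with mean m and size k, so variance = m + m²/k. The control mean is 2, 5 or 10, k is 0.7 or 1.5, and the reduction is 80% or 60%. The Discussion remarks that a cited author "he observed little frequency of ballooning cells", so the low end of this range may be the more relevant one.

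**Why presence loses information.** The chance that a slide shows at least one cell is 1 − (k/(k + m))^k. Take m = 10, k = 1.5 and an 80% reduction, so the treated mean is 10 × 0.2 = 2:

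- control: 1 − (1.5/11.5)^1.5 = 0.953, or 12 × 0.953 = 11.4 positive slides expected of 12;
- treated: 1 − (1.5/3.5)^1.5 = 0.719, or 12 × 0.719 = 8.6 of 12.

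A five-fold fall in the mean count becomes a difference of about three positive slides.

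**Power, 80% reduction.** Simulation, 4,000 trials per row, 12 per arm; t test on counts, Fisher's exact test on presence.

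| k | Control mean | Count | Presence |
|---|---|---|---|
| 0.7 | 2 | 49% | 28% |
| 0.7 | 5 | 61% | 22% |
| 0.7 | 10 | 66% | 13% |
| 1.5 | 2 | 72% | 44% |
| 1.5 | 5 | 89% | 33% |
| 1.5 | 10 | 94% | 13% |

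Repeat runs move the ends by a point or two; the summary range is about 48% to 95% for the count against about 13% to 42% for presence. For a 60% reduction the count has about 22% to 60% and presence about 1% to 14%. A rank test on the counts gives about the same power as the t test (50% to 92% for the 80% reduction), so the gain comes from using the count and not from the choice between those two tests.

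**How the forms disagree.** In a separate simulation with k = 1 and means of 10 v 4, 6 v 2 and 3 v 1, one form was significant and the other not in 41%, 45% and 32% of trials. The two estimates pointed in opposite directions in 14%, 8% and 6%. In the scenarios with k = 0.7 or 1.5, both forms were significant in opposite directions in 0 trials.

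**Timing.** Section 2.12 dates the second slide from injury, while the cytokine, pain, temperature and OHIP-14 items in the same list are dated from treatment. Both the overview and the ballooning-cell item attach the label T1 to day 3, and the overview makes T1 a return visit. Section 2.7 places the baseline collection before treatment, with treatment following it.

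**The case against.** **Presence may be a loose label.** Section 2.12 also speaks of the presence of pain, which section 2.13.10 measures on a 100 mm line. Section 2.13 holds the detailed definitions, and its verb is to quantify. The t test of means points the same way. This has force: a count is the likelier intention. It does not settle the matter, because the Discussion treats cytology as a means of confirming HSV infection, which is a presence use, and no unit of counting is given.

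**The sizes are assumed.** That is so. They show that the choice of form can matter a great deal at 12 per arm; they do not predict this trial's power.

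**Analysis detail belongs elsewhere.** The exact model may be left to a fuller plan. The contradiction over what the outcome is stands within this article.

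**Two stronger readings are not supported.**

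- A reader might infer that the two forms could give significant results in opposite directions. Such a dataset can be constructed: 11 of 12 positive with mean 1.1 against 5 of 12 positive with mean 8.3 gives Fisher P = 0.027 one way and t test P = 0.038 the other. It needs a contrived pattern, and the simulated scenarios checked for it produced none.
- A reader might infer from the words after injury that the second slide of a patient who enters at the crust stage could precede treatment. The T1 label rules this out, since T1 is the return visit at 3 days. The article also uses injury as a word for the lesion, so this is a slip of wording. It cannot affect how a given slide is read.

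**Conclusion.** The point holds as a minor one. The article gives one secondary outcome in two forms, and its only stated test fits one of them. The consequence is that the same slides may be significant as a count and not significant as presence. Under the assumed counts, power for an 80% reduction is about 48% to 95% against about 13% to 42%. These figures rest on negative-binomial counts with control means of 2 to 10 and k of 0.7 to 1.5, none of which the article supplies. The primary outcome and the sample size are not affected.

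**What to change.** - **One form in sections 2.12 and 2.13.3:** the number of ballooning cells per fixed number of epithelial cells on the slide, at T0 and T1.
- **Comparison:** compare the arms at T1, adjusting for the T0 count already collected, for example on a log or count scale. The extra precision from the adjustment was not quantified here.
- **Presence:** report it descriptively only, including at T0 where it serves to confirm infection.
- **Wording:** in section 2.12, date the second slide as 3 days after treatment (T1). This changes no procedure.

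The slides are already planned at both visits, so the cost is wording in two sections and a little more counting time per slide.
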